## Oversight and monitoring

### Oversight committees

The study will be overseen by two oversight committees: the TSC and a Data Monitoring and Ethics Committee (DMEC). The TSC will be chaired by an independent expert and will be responsible for monitoring progress of the study and reviewing amendments to the trial protocol. Committee members will include experienced clinicians, commissioners of forensic mental health services, criminal justice professionals, and service user representatives. A group of clinicians with relevant experience in the area and expert trial statisticians will form the independent DMEC, which will be responsible for monitoring recruitment and follow-up rates across both arms of the trial, as well as serious adverse events (SAEs) and ethical concerns. Minutes from the DMEC will be shared with the TSC chair following each meeting, and the TSC will report directly to the funder.

### Adverse events

For this study, adverse events will be defined as immediate risk of harm to the participant or another person and will be collected after the participant has provided consent and enrolled in the study. Each event will be logged by the research team following contact with the participant and regularly reviewed by the Research Manager, Clinical Lead, and Chief Investigator. If an adverse event meets the criteria for a serious adverse event (SAE) between study enrolment and the 24-month data collection time point, the event will be logged and reported to the DMEC for review. SAEs occurring after a participant is discontinued from the study will not be reported unless the investigators feel that the event may have been caused by a study protocol procedure.

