#### Randomization and procedures to minimize bias

Following consent and baseline measures, a trial identification number will be assigned to eligible consenting participants and a recruitment ‘dam’ created behind which a participant pool will be built up, from which participants will be randomized to enable MBT groups to start. Once groups have started, sequential assignment will allocate participants to MBT or PAU in a 1:1 ratio. Randomization will be undertaken off-site, using a dynamic adaptive allocation algorithm [76] accessed by a secure web portal to the system held at NWORTH Clinical Trials Unit (CTU) and maintained by a statistician independent of the analysis and research teams to ensure blinding. Stratification will be by site, age (21–25; 26–39; 40+ years), probation order type (Community Sentence; On Licence Post-Prison), and time remaining on probation (less than 12 months; 12 months and over). Treatment site is included in the minimization stratification to control for differences between sites. To minimize bias that could arise from knowledge of treatment allocation, researchers will be blind to participants’ treatment. The allocation to treatment arms will not be modified unless the local principal investigator, with the agreement of the clinical supervisor or the Trial Steering Committee (TSC), identifies severe risks of adverse events (homicide, suicide, serious injury, etc.) associated with the experimental treatment. Experimental treatment will be discontinued if the participant breaks the conditions of probation and is recalled to serve the remainder of their prison sentence for a time which prevents any further attendance or if the participant commits further offences and receives a custodial sentence for the fresh conviction that is longer than the remaining time of treatment.

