#### Objective measures

Objective outcomes of health service use will be collected from record linkage using participants’ NHS numbers at 6-monthly intervals during the intervention and the follow-up period until the 24-month follow-up point.

Objective outcomes of offending behaviour, including withdrawal of licence, arrests, and reconvictions, will be collected from police computer records at 6-monthly intervals, for the 6 months before randomization and during the intervention and follow-up period until the 24-month follow-up point. The number of records of offending behaviour (count data) will be obtained, and 6-month periods free of any offending behaviour will also be recorded (binary data). Data will be obtained from participants’ records on nDelius (the national public sector offender case-management system) and the Police National Computer database; these records detail information on breaches of licence conditions, police contacts, charges, court appearances, criminal orders, arrest rates, and frequency, severity, and type (violent/non-violent) of offending behaviour.

These objective outcomes of health service use and offending behaviour will be available regardless of loss to follow-up; this will allow the use of multiple imputation techniques. If loss to follow-up is considerably different between arms and the primary outcome is significant, we will perform a sensitivity analysis to the impact of missing data not being missing at random, as described by White et al. [80].

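### The adverse-event definition covers immediate risk of harm and leaves it unclear whether completed serious harm is inside the safety system that the DMEC reviews

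*Protocol article*

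**What the plan says.** Four parts of the protocol article bear on this.

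- **Definition** (Adverse events): "adverse events will be defined as immediate risk of harm to the participant or another person". Harm that has already occurred is not named.
- **Capture** (same section): "Each event will be logged by the research team following contact with the participant". No other source is mentioned there.
- **Serious events** (same section): the condition for logging and reporting to the DMEC begins "If an adverse event meets the criteria for a serious adverse event (SAE) between study enrolment and the 24-month data collection time point". The serious category is therefore drawn from events that already count as adverse events. The criteria themselves are not printed. The section also limits late reporting: "SAEs occurring after a participant is discontinued from the study will not be reported unless the investigators feel" that a study procedure may have been the cause.
- **Another use of the term** (Randomization and procedures to minimize bias): allocation is not modified unless the local principal investigator, with the agreement of the clinical supervisor or the Trial Steering Committee, "identifies severe risks of adverse events (homicide, suicide, serious injury, etc.) associated with the experimental treatment".

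Under Oversight committees, the DMEC monitors recruitment and follow-up in both arms, "as well as serious adverse events (SAEs) and ethical concerns".

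**The concern.** One section makes an adverse event a state of risk; the other makes it a harm that has happened. Both are stated rules, so this is not a detail lost when the full protocol was condensed.

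Assessments are 3 months apart. A serious assault or suicide attempt two months before an interview is a past event when it is disclosed, and a literal reader could decide that it is no longer an immediate risk. A death cannot be followed by contact with the participant. A man recalled to prison or lost to contact may give the research team nothing to log.

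At stake is what the DMEC sees. If the log is kept to the letter, the committee reviews current risk among men who can be reached, and may not see completed harms by arm. In a trial of a treatment for aggressive men, a safety summary built that way would tend to count too few events.

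**Working it through.** No figure in the article depends on the definition, so the check is mainly a comparison of text.

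**Step 1: meaning of the term.** Under Adverse events, the term means an immediate risk of harm. In the randomization section, its examples are homicide, suicide and serious injury. Putting the first definition into the second sentence gives a severe risk of an immediate risk of harm, which is not a workable meaning. The sections cannot both be using the same definition.

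**Step 2: whether the SAE tier repairs the gap.** The sequence is adverse event, then the serious criteria, then the DMEC. Whatever the unprinted criteria contain, they apply only to events that have passed the first test. A good list of serious criteria would not bring in a completed harm that the definition had left out.

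**Step 3: whether the capture route repairs it.** The stated route needs contact with the participant. It cannot operate after his death and may fail after recall to prison or loss of contact. Offender Managers and MBT clinicians, who may hear of events first, are not named as sources.

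**Step 4: whether other data cover it.** Partly. Under Objective measures, "Objective outcomes of offending behaviour, including withdrawal of licence, arrests, and reconvictions, will be collected from police computer records at 6-monthly intervals", and "These objective outcomes of health service use and offending behaviour will be available regardless of loss to follow-up". The Overt Aggression Scale – Modified, the MacArthur violence instrument, the Self-Harm Inventory and the Suicidal Behaviours Questionnaire are also scheduled. All are described as outcomes, and none is said to feed the adverse-event log or the DMEC. The health linkage is described as service use; the article does not say whether it returns deaths.

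**Step 5: how many men might be out of contact.** This is context, not an estimate of missed events.

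- Planned attrition (Sample size and power calculation) is 37%, with 95 per arm needed. 95 / (1 − 0.37) = 150.8, rounded up to 151 per arm, which reproduces the article's 302.
- Expected loss at 37%: 302 − 2 × 95 = 112 men.
- Expected loss at the one third reported so far (Discussion): 302 / 3 = 100.7, about 101 men.
- Recall to prison is given as the reason for 35% of dropouts: 0.35 × 101 = 35 men, if that share held for the whole trial.
- Clinicians' discretion over missed MBT sessions accounts for 7%: 0.07 × 101 = 7 men, all necessarily in the MBT arm.

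The range of 101 to 112 treats every dropout as lost to research contact. The article does not say this, and it plans follow-up of everyone who does not formally withdraw. The range is therefore an upper one. If the 7 men in the last line also lost contact or counted as discontinued, ascertainment could differ slightly between arms; the article does not settle that either.

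**The case against.** The strongest reply is that the section plainly intends realised events. It speaks of SAEs occurring after discontinuation and asks whether the event may have been caused by a study procedure, which is language for things that happen. It also presupposes that investigators can learn of events after a man has left, so participant contact may be the usual workflow and not an exclusive route. The serious criteria probably stand in the full protocol, and their absence from the article is no fault. Most of this stands as evidence of intent. It does not remove the stated definition or the order in which the tests apply.

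Three stronger readings are tempting, and the article does not support them.

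- **Deaths are never captured.** A reader might infer this from the contact route. Other sources are not barred, and the wording on SAEs points the other way. Capture of deaths is unclear, not shown to be nil.
- **Dropouts go unlogged for most of the 24 months.** A reader might infer this from the reported 3 to 6 months of engagement before dropout. Men who do not formally withdraw are still followed. The randomization section ties recall to stopping treatment, not to ending follow-up.
- **The rule on modifying allocation depends on the log.** That rule turns on severe risks as judged by the local principal investigator with the agreement of others. Nothing routes it through the adverse-event log, and a risk-based definition partly suits it.

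It is also fair to say that harms are measured in both arms as outcomes, so the trial as a whole would not be blind to them.

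**Conclusion.** The point holds as an inconsistency between two stated uses of the term, with a practical consequence for safety monitoring. Read literally, the adverse-event section does not clearly admit completed serious harm, and the serious tier that goes to the DMEC inherits that limit. The doubt is greatest for deaths and for events in men out of contact.

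The number of events that would be missed cannot be derived from the article. The only size available is the upper range of 101 to 112 of 302 men who might at some time be out of contact, on the assumption that dropout means loss of research contact.

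The conclusion rests on taking the definition as written and on the absence of any stated link from the outcome data to safety reporting. If the full protocol defines adverse events to include realised harm and names further sources, the article only needs to be brought into line with it. The wording should be changed in either case, because it governs what an independent committee is shown.

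**What to change.** 1. Reconcile the adverse-event section with the randomization section, so that an adverse event includes actual harm since the last contact (death, suicide attempt or serious self-harm, serious injury, serious violence to others) as well as immediate risk. Who decides on allocation, and on what grounds, is a separate clinical matter and is not addressed here.
2. State that events may be logged from any source: the participant, the Offender Manager, the MBT team, and the police and NHS records already extracted. Say explicitly how deaths are ascertained.
3. Tabulate the events by arm for the DMEC with the same rule in both arms. Show the source of each report, because the MBT team has treatment contact with one arm only and could otherwise raise that arm's count through closer observation.
4. Send reports from the MBT team to staff who are not blinded outcome assessors. The Economic evaluation section already collects MBT contacts directly from sites to protect blinding, so the same separation is practicable.

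The cost is a change of wording and use of data already being collected. The Trial status section says that follow-up was still in progress, so records could still be tabulated. The downsides are more events to log and review, some overlap with the aggression and violence outcomes (which should be acknowledged when harms are reported), and the extra reporting line needed to preserve blinding.

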## Dissemination policy

The results of the study will be disseminated through publications in peer-reviewed journals as well as presentations, newsletters, and articles for the probation and prison system and third sector organizations working within the criminal justice system.

## Discussion

This study will address key gaps in the offending and health literature. To date, there have been very few high-quality trials with a sufficiently powered sample size that have evaluated therapeutic interventions for offenders with a primary diagnosis of ASPD. The MOAM trial is the first large-scale trial of treatment for offenders with ASPD in the community and has a number of strengths compared with other trials of interventions for antisocial behaviour. First, it is a definitive RCT, conducted in real-life community settings, at multiple sites with a representative geographical spread and a range of clinicians from diverse disciplinary backgrounds. Second, the sample size is sufficient to yield 90% power, even after accounting for a potentially high attrition rate. Third, its sample is selected on the primary diagnosis of ASPD as fully differentiated from other mental health conditions. Fourth, the trial design incorporates the innovative use of peer researchers as a strategy to enhance the accuracy and validity of participant data. Finally, the measures employed will enable us to look beyond recidivism and will capture the effects of MBT on a wide range of secondary health and behavioural outcomes, including diagnostic change of ASPD itself.

Aggressive antisocial behaviour has been chosen as the primary outcome for this trial, in light of it being a core feature of ASPD, an indicator of emotional wellbeing, and a frequent cause of grounds for arrest. A range of secondary outcomes have also been chosen in order to evaluate MBT’s possible impact on the wide range of symptomatology and health outcomes experienced by individuals with ASPD, including impulsivity, offending behaviour, alcohol and substance misuse, self-harm and suicidality, and general health and wellbeing. The MOAM trial will also provide accurate information about the services accessed under PAU. A comprehensive cost-effectiveness evaluation will be undertaken to examine both costs offset and costs saved in relation to having received MBT or PAU. Thus, the trial will provide unprecedented data not only on the clinical effectiveness and cost-effectiveness of MBT-ASPD, but also on the clinical effectiveness and cost-effectiveness of the usual services available to this group while on probation. Furthermore, the trial will analyse offender referral information to identify trends, calculate the size of the population likely to benefit from an intervention for ASPD, and make recommendations about treatment groupings and targeting of services.

Information to date suggests that the trial protocol detailed above is acceptable to all the sites and that recruitment, data collection, and training are feasible in all locations. Preliminary data on participant engagement indicate that, of participants randomized to MBT, an average of 55–65% attend group MBT sessions. Preliminary data indicate that one third of participants drop out at some point following randomization, entirely consistent with attrition rates reported in other studies involving treatment for offenders and patients with personality disorders [70–72]. For participants who drop out, the average length of engagement with the trial is 3–6 months; the most common reasons for dropout thus far are lack of motivation (58%), recall to prison (35%) and clinicians’ discretion due to repeated non-attendance of MBT sessions (7%).

The authors acknowledge that there is such a scarcity of evidence for effective interventions for ASPD that additional trials are greatly needed. Beyond the completion of the MOAM trial, the authors recommend further high-quality RCTs incorporating the following adaptations: minimal involvement of the intervention developers, to minimize bias; a female sample, to improve generalizability of results; longer-term follow-up, to determine whether differential effects are maintained; and investigation of the impact of differences in clinicians’ training, experience, and supervision, to determine minimal training and supervisory standards and competences for effective delivery of treatment.

## Trial status

The trial is in its fifth year. Sites were launched in four phases between January and September 2016, and recruitment ended in August 2018. Treatment and follow-up data collection are currently in progress. The protocol paper was submitted after the end of recruitment as the outcome frequency of aggressive antisocial behavior is measured at the last follow-up meeting 24 months post-randomization. Outcome data will be available 12 months post-randomization of the last participant.

*Trial protocol version:* v6.0, 2 December 2018.

## Data Availability

Not applicable.

## Abbreviations

ASPD: Antisocial personality disorder
AUDIT: Alcohol Use Disorders Identification Test
BPD: Borderline personality disorder
CTU: Clinical Trials Unit
DMEC: Data Monitoring and Ethics Committee
DUDIT: Drug Use Disorders Identification Test
MBT: Mentalization-based treatment
MBT-ASPD: Mentalization-based treatment for antisocial personality disorder
NICE: National Institute for Health and Clinical Excellence
NPS: National Probation Service
OAS-M: Overt Aggression Scale – Modified
PAU: Probation as usual
PID-5-BF: Personality Inventory for DSM-5–Brief Form
QALY: Quality-adjusted life year
POD: Patient Owned Database
RCT: Randomized controlled trial
SAE: Serious adverse event
SCID: Structured Clinical Interview for DSM-IV
SCL-90-R: Symptom Checklist-90 – Revised
SOM: Specialist Offender Manager
STAXI-2: State-Trait Anger Expression Inventory-2
TSC: Trial Steering Committee
